#### 7.1.9. Time Period, and Frequency of Detecting AEs and ARs

From the time a subject consents to participate in the study until he or she has completed the study (including any follow-up period), all SAEs assessed as related to study participation (e.g., protocol-mandated procedures, invasive tests, or change in existing therapy) will be reported promptly to the principle investigator.

#### 7.1.10 Reporting of Serious adverse reactions

Adverse events will be reported according to the National Research Ethics Service requirements for recording, managing and reporting Adverse Events and Adverse Reactions in Clinical Trials. In particular, on receipt of a SUSAR report the CI will immediately notify [name], Research and Business Services by sending a copy of the SAE Form by email to the Sponsor's representative so that the necessary reporting by the Sponsor can take place within the deadlines.

## 8 Data Evaluation

The endpoints to be measured are:

- *Primary endpoints*
  - Total nasal symptom score 10 minutes following nasal allergen challenge.
- *Secondary endpoints*
  - Area under the curve for nasal symptoms scores for 12 hours following nasal allergen challenge
  - Area under the curve for peak nasal inspiratory flow for 12 hours following nasal allergen challenge
  - Phenotype of nasal epithelial cells from scrapings
  - Nasal lavage inflammatory mediator profile

Data analysis and decoding will be performed by simultaneous exchange of raw data and code exchanges between the principal investigator and Yakult

All manuscripts arising from this study will be offered to Yakult for pre-publication perusal. Publicity of results will be conducted in accordance with the policies of the Institute of Food Research, University of East Anglia and Norfolk and Norwich University Hospitals NHS trust. Publication of the results will be in the peer-reviewed literature and at national and international meetings. The results may also be featured in press and trade articles. At the end of the study, following data evaluation, all study participants will be invited to attend a small 'get together' when the study findings will be revealed to them.

## 9. Statistical evaluation

The primary clinical end-point will be considered to be total allergic rhinitis symptom scores. Using total allergic rhinitis symptom score as the response variable and treatment, subject and time as explanatory factors, a repeated measures ANOVA will be used to analyse the data including time as a random effect also treatment group, baseline score and variables used in stratification will be included as fixed effects. Any significant effects for the factors will be investigated further by TukeyHSD (post-hoc analysis) to ensure that the type 1 error rate remains at 5%. Similar ANOVA models will also be used to study the effect of the other measured response variables (e.g. nasal PIFR ) against treatment. In addition, a canonical

discriminant analysis may be performed to unravel the complex immunological interactions taking place.

Analysis of time-to-event data will be analysed using the log-rank test to compare between groups and the proportional hazards model will be used if it proves necessary to adjust for baseline measures. The analysis will be stratified by variables used to stratify the randomisation procedure.

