| Site and subjects    | 60 adult subjects (30 in each of two groups). All study procedures involving participants will be conducted within the Clinical Research Trials Unit (CRTU) at the Norfolk and Norwich University Hospital (NNUH). Samples taken will be processed at both UEA and IFR. Inclusion/exclusion criteria are detailed below. Summarised: men and women >16 years of age with a history of seasonal allergic rhinitis.                                                                                                                                                                                                                  |
| Procedures           | The study aims to examine the effect of probiotics on the clinical symptoms of allergic rhinitis and to elucidate some of the immunological mechanisms involved. Following a screening procedure, enrolled participants will undergo nasal allergen challenge when their baseline clinical and immunological responses will be measured. Participants will then be randomized on a 1:1 ratio to receive probiotic or placebo formulation. They will consume these for a period of 4 months after which they will return for a further nasal allergen challenge and post-treatment clinical and laboratory assessment of responses. |
| Primary endpoints    | Total nasal symptom score (TNSS) 10 min after nasal allergen challenge.                                                                                                                                                                                                                                                                                                                                                                                                                                                                                                                                                            |

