| Secondary endpoints  | 

• Area under the curve for nasal symptoms scores for 12 hours following nasal allergen challenge

• Area under the curve for peak nasal inspiratory flow for 12 hours following nasal allergen challenge

• Phenotype of nasal epithelial cells from scrapings

• Nasal lavage inflammatory mediator profile

                                                                                                                                                                                                                                                  |
| Statistical analysis | Sample size calculated based on 46 participants providing 90% power to detect a treatment difference at a two sided 5% significance level, if the true difference between the treatments is a TNSS of 1.5 following allergen challenge based on the assumption that the standard deviation of TNSS following nasal allergen challenge is 1.5 (Dreskin et al 2002). Sixty participants will be enrolled to allow for 20% drop-out.                                                                                                                                                                                           |

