Procedure 2 involves participant visits on two consecutive days. This will involve nasal samples being obtained before and 24 hours after the nasal allergen challenge. At the first of the 2-day procedure (visit 2), participants will have a clinical examination, and baseline nasal and total allergic rhinitis symptoms scores, nasal peak inspiratory flow, nasal scrapings and nasal lavage. 20ml blood will be taken for laboratory analysis. They will then undergo a nasal allergen challenge and record their nasal symptoms and peak nasal inspiratory flow at 5 mins, 30 mins then hourly for 12 hours. A nasal lavage will be collected at 30 mins. Asthmatic participants will undergo spirometry prior to and 1 hour following the nasal allergen challenge. They will also record asthma symptom scores prior to the challenge and hourly following the challenge. Those participants able to return after 6-8 hours (visit 3) to give a nasal lavage, peak nasal inspiratory flow (PNIF) and asthma symptom scores (ASS) and spirometry in asthmatic participants. These subjects will form a subgroup. All participants will return for the 24 hours later (visit 4) following the nasal allergen challenge, for a second nasal scraping and lavage. 20 ml peripheral blood will be taken at this time for laboratory analysis. Following this, participants will be randomized to active drink or similar placebo daily for 4 months. Procedure 2 will take place at least 2

weeks after procedure 1 and no later than November. Participants with isolated grass pollen allergy will attend for procedure 2 no later than December 20~~10~~.

Procedure 3: Post-intervention follow-up measurements ~ participant visits 5, 6 and 7

Procedure 3 involves participant visits on two consecutive days when they will undergo follow-up assessment identical to procedure 2. Procedure 3 will take place 4 months following procedure 2 and no later than March 201~~0~~. Participants with isolated grass pollen allergy will attend for procedure 3 no later than April 201~~0~~.

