### 6.2 Total Nasal Symptom Scores (TNSS)

Following exposure to allergen, there is an immediate rise in the reported symptoms. The magnitude of these symptoms changes with time, and the recording of the symptoms scored at various time points is referred to as the TNSS. Participants will be asked to record their symptoms on a 4 point scale, with 0 representing no symptoms and 3 representing maximal symptoms:

0 = absent symptoms (no sign/symptom evident)

1 = mild symptoms (sign/symptom clearly present, but minimal awareness; easily tolerated)

2 = moderate symptoms (definite awareness of sign/symptom that is bothersome but tolerable)

3 = severe symptoms (sign/symptom that is hard to tolerate; causes interference with activities of daily living and/or sleeping)

Symptoms will be recorded under the following;

- ~ Sneezing
- ~ Itching
- ~ Rhinorrhoea
- ~ Congestion

The individual symptoms will be summed to give a total nasal symptom score with a maximum value of 12 (Dreskin *et al.* 2002).

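### Section 9 names a different primary endpoint and test from the TNSS at 10 minutes that the synopsis and Section 8 define, and the sample size was not derived for it

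*Protocol*

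**What the plan says.** Three places in the protocol bear on the primary endpoint.

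- **Synopsis, primary endpoints:** "Total nasal symptom score (TNSS) 10 min after nasal allergen challenge".
- **Section 8, Data Evaluation:** "Total nasal symptom score 10 minutes following nasal allergen challenge". The 12-hour course of nasal symptoms appears here as a secondary endpoint, summarised as an area under the curve.
- **Section 9, Statistical evaluation:** "The primary clinical end-point will be considered to be total allergic rhinitis symptom scores". The model follows: "Using total allergic rhinitis symptom score as the response variable and treatment, subject and time as explanatory factors, a repeated measures ANOVA will be used". Baseline score and the stratification variables are added as fixed effects. No time point is named.

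The synopsis sizes the trial for 90% power at two-sided 5% with 46 participants, "if the true difference between the treatments is a TNSS of 1.5 following allergen challenge", and an SD of 1.5. Sixty are enrolled to cover 20% drop-out.

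On the scores themselves, Section 6.2 defines TNSS from four symptoms scored 0 to 3: "The individual symptoms will be summed to give a total nasal symptom score with a maximum value of 12". Section 5.1 lists "baseline nasal and total allergic rhinitis symptoms scores" among the Procedure 2 measurements, which reads as two scores. Section 6 defines TNSS, an asthma symptom score and peak nasal inspiratory flow. It gives no items, range or scoring rule for an allergic rhinitis score.

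**The concern.** Section 9 is the only section that says how the endpoints will be tested, and it differs from the endpoint definition in two ways: the name of the score, and one time point against repeated times. A reader following Section 8 and a reader following Section 9 would run different primary tests and could reach different conclusions.

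Two things are at stake. First, the primary hypothesis test is not uniquely fixed, so the protocol does not itself rule out settling the question after results are known. Second, the 90% power was worked out for a difference in TNSS. If Section 9 governs, the trial has no stated sample size justification for its primary analysis.

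**Working it through.** **1. Reproduce the stated sample size.** Inputs from the synopsis: difference 1.5, SD 1.5, two-sided alpha 0.05, power 0.90, 1:1 allocation. The standardised difference is 1.5 / 1.5 = 1.0.

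- Normal approximation: n per arm = 2 × (1.960 + 1.282)² / 1.0² = 21.01, rounded up to 22, or 44 in total.
- Two-sample t test (noncentral t, noncentrality 1.0 × √(n/2)): 22 per arm gives 89.97% and 23 per arm gives 91.2%. So 23 per arm, 46 in total, is the first size to reach 90%.
- Drop-out: 46 / (1 − 0.20) = 57.5, rounded up to 58. The planned 60 covers this.

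The stated 46 and 60 are sound for a single TNSS comparison. The sample size sentence says only that TNSS is measured after challenge. The link to 10 minutes comes from the endpoint definitions in the synopsis and Section 8.

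**2. Set the two primaries side by side.**

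| | Synopsis and Section 8 | Section 9 |
|---|---|---|
| Score | TNSS | Allergic rhinitis score |
| Defined in Section 6 | Yes, 0 to 12 | No |
| Time | 10 minutes after challenge | Not stated; time is a model factor |
| Test implied | One post-challenge value per participant | Repeated-measures ANOVA |
| Difference and SD for sizing | 1.5 and 1.5 | None given |

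**3. Is the score the same?** The protocol points both ways. Section 5.1 names two scores. The schedule in Section 5.2 puts nasal and allergic rhinitis scores in one combined row. Sections 5.2.1, 5.10.1, 5.10.2 and 5.10.6 list only TNSS, and Section 6.2 defines only TNSS.

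**4. Does the conflict survive if the score is the same?** Yes. A model with time as a factor uses more than one time per participant. The Section 8 endpoint is one value at one time, and Section 8 places the longer symptom course among the secondary endpoints.

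**5. Can the power of the Section 9 analysis be computed?** No. If the score differs from TNSS, its range, SD and target difference are all missing. If it is TNSS, the protocol still gives no list of times in the model, no correlation between times, no SD at later times and no expected effect at later times.

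**6. Is the 10-minute value collected?** Section 6.6 records symptoms at 10 minutes, 30 minutes and then hourly for 12 hours. Section 5.1 gives 5 minutes, 30 minutes and then hourly for Procedure 2, and says that Procedure 3 is identical. Under the Section 5.1 schedule there is no 10-minute recording.

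**The case against.** The strongest reply is that Section 9 is loosely worded and means TNSS. Most procedure lists name only TNSS, and no other rhinitis score is defined. That reading is plausible, so the documents do not establish that a second scale exists. It settles the name but not the conflict between one time and repeated times.

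A second reply is that the synopsis and Section 8 agree, and a statistical analysis plan may settle the matter. It may. But this is a contradiction between stated primaries, not a detail left for later: a plan faithful to Section 8 would depart from Section 9, and the reverse.

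Several stronger readings are tempting, and the documents do not support them.

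- **That power under Section 9 is known to be poor.** Suppose the test averages the 14 times in Section 6.6, with assumed effects of 1.5 at 10 minutes, 1.0 at 30 minutes and 0.5 at each hour. The mean effect is (1.5 + 1.0 + 12 × 0.5) / 14 = 0.607. With 23 per arm, SD 1.5 throughout and correlation 0.5, the SD of the mean is 1.5 × √((1 + 13 × 0.5) / 14) = 1.098, and power is 45%. Correlation 0.2 gives an SD of 0.761 and 75%. Correlation 0.5 with an hourly SD of 0.75 gives an SD of 0.629 and 89%. Every one of these inputs is an assumption, the baseline covariate is left out, and Section 9 does not say that the test is an average over 12 hours. The spread shows that power is undetermined, not that it is low.
- **That TNSS at 10 minutes would go unanalysed.** Section 9 applies similar ANOVA models to the other measured responses, which could include it.
- **That the areas under the curve, such as "Area under the curve for peak nasal inspiratory flow for 12 hours following nasal allergen challenge", have no analysis.** The same sentence could cover them, and the details can be left to an analysis plan.

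**Conclusion.** The protocol states two incompatible primary analyses, and this should be corrected before any unblinded analysis. The conflict over time point is certain from the text. The conflict over the score is probable but could be loose naming.

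The size of the problem is that the primary test is not uniquely defined, and the 90% power (91.2% on recalculation with 46 evaluable) applies only to the TNSS version. No power figure for the Section 9 version can be taken from the protocol.

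A reader might infer that the endpoint will be picked after the data are seen. The text leaves that open as a risk but gives no evidence of such an intention. A reader might also take the correction to be free of any data question. It is not, because Section 5.1 and Section 6.6 disagree on whether the first recording is at 5 or 10 minutes.

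**What to change.** Amend Section 9 so that:

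1. the primary endpoint is TNSS, as defined in Section 6.2, at 10 minutes after the Procedure 3 challenge;
2. the arms are compared on that value with adjustment for the corresponding Procedure 2 TNSS and the randomisation strata, the kinds of covariate Section 9 already names;
3. the repeated-times symptom analysis is secondary, with its score named and defined.

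In the same amendment, reconcile the first post-challenge recording time between Sections 5.1 and 6.6, so that the primary value is collected at both challenges. If an allergic rhinitis score separate from TNSS is kept, add its items and range to Section 6; otherwise remove the term.

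The cost is wording in the protocol and in any analysis plan. The sample size of 46 evaluable and 60 enrolled stands. Before relying on the change for participants already challenged, check which first recording time was actually used.

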#### 5.10.3 *Intervention and delivery schedule*

Participants will be randomised on a 1:1 ratio to receive probiotic or placebo formulation. Samples of the milk drinks, active or placebo, will be delivered by Yakult Europe B.V to IFR Norwich every 2 weeks. The samples will be HACCP certified for the safety of materials, production process and microbiological analysis (issued by TNO, Holland). The active and placebo drinks will be identical in composition except for inclusion of  $6.5 \times 10^9$  LcS organisms per 65ml of dairy drink. Volunteers will be supplied with probiotic or placebo milk drinks every 2 weeks throughout the 4-month intervention period. These samples will be distributed to the subjects by IFR Norwich.

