#### 6.6 Modified Intranasal allergen challenge

Nasal allergen challenge is a non-invasive method used to study pathophysiological mechanisms in rhinitis. Normally a single high dose of allergen is sprayed into the nose to induce an allergic response. We have modified this test so that we will first find an optimum dose that will induce a certain fixed level of response for each participant. That individual dose will then be used in the study. We believe this will avoid any adverse events and will improve our study since all participants will start the study at the same maximum response. Changes from this will be monitored following intervention.

Subjects will be asked to refrain from anti-histamine use for at least 3 days leading up to the Day 1 assessments. A modified challenge will be performed (Dreskin *et al.* 2002). The concentration of allergen identified in the allergen challenge performed during procedure 1 (screening visit) will be administered at 0.1ml using a pump spray. Nasal symptoms (based on a combination of nasal symptoms including nasal obstruction, itching, sneezing, and rhinorrhoea) will be recorded at 10 minutes, 30 minutes then hourly for 12 hours. PnIF will be measured prior to allergen challenge 10 minutes, 30 minutes, and hourly for 12 hours.

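### Section 9 makes time the random effect and gives subject no defined role, so the stated repeated-measures model does not secure a valid treatment test

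*Protocol*

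**What the plan says.** Section 9 takes the symptom score as the response, with "treatment, subject and time as explanatory factors". It continues that "a repeated measures ANOVA will be used to analyse the data including time as a random effect", and then lists treatment group, baseline score and the stratification variables as fixed effects. Subject appears in the first list only. Time is the only factor called random. No error term or within-subject covariance is given. Similar ANOVA models are to be used for the other responses, and Tukey's procedure is relied on to hold the type I error at 5%.

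Two other places bear on this:

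- **Section 6.6.** Nasal symptoms after the modified challenge "will be recorded at 10 minutes, 30 minutes then hourly for 12 hours". The times are therefore set by design.
- **Section 5.10.3.** "Participants will be randomised on a 1:1 ratio to receive probiotic or placebo formulation". Treatment is thus constant within a participant during follow-up.

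The Synopsis and Section 8 define the primary endpoint as the total nasal symptom score (TNSS) at the single 10-minute point. Section 9 does not say which times enter its model.

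**The concern.** In a repeated-measures analysis the random part of the model decides what the treatment difference is compared with. Treatment varies between participants, so the yardstick must be variation between participants, and a random subject effect or a within-subject covariance provides it. A random effect for time does not. It says that all participants share a shift at a given time, and nothing about scores from one person resembling each other. The 10-minute, 30-minute and hourly points are also not a sample from a population of times, and symptoms are expected to follow a systematic course over them.

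This is more than a detail left for a statistical analysis plan. The sentence assigns roles and gives the random one to the wrong factor. It is the only model the protocol offers for what Section 9 calls the primary clinical endpoint. If it were programmed literally over the 12-hour profile, the main efficacy test could reject far more often than 5% under no effect. Tukey's procedure adjusts for the number of comparisons and cannot repair a wrong error term.

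**Working it through.** **Inputs from the protocol**

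- Size and power (Synopsis): "Sample size calculated based on 46 participants providing 90% power to detect a treatment difference at a two sided 5% significance level".
- Difference: "if the true difference between the treatments is a TNSS of 1.5 following allergen challenge".
- Standard deviation: "the standard deviation of TNSS following nasal allergen challenge is 1.5".
- Enrolment: "Sixty participants will be enrolled to allow for 20% drop-out".
- Scores per person after one challenge (Section 6.6): 10 minutes, 30 minutes and 12 hourly points, so 1 + 1 + 12 = 14. Section 5.1 gives 5 minutes as the first point; the count is the same.

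**Assumption.** The correlation ρ between two scores of the same person, after covariate adjustment, is not in the protocol. The range 0.1 to 0.7 is used, with equal correlation between all pairs of times.

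**1. The protocol's own figure.** With the normal formula, n per arm = 2(1.96 + 1.2816)² × (1.5/1.5)² = 21.01, rounded up to 22, or 44 in total. The t-test needs 22.02, so 23 per arm and 46 in total, with power 0.912. For drop-out, 46/0.8 = 57.5, so 58 against the 60 planned. The 46 is reproduced. It rests on one value per participant and so does not depend on the repeated-measures model.

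**2. Subject as a fixed factor.** The intercept and 45 subject indicators use 46 columns, and 13 time indicators bring this to 59. Treatment (1), baseline (1) and four strata (3) add five, giving 64 columns. All five are constant within a person and are therefore linear combinations of the subject columns. The rank, checked numerically, stays at 59, so the treatment effect is not estimable.

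**3. Time as the only random effect, no subject term.** With balanced data the time effect cancels from the treatment comparison, so treatment is tested against a residual that treats 46 × 14 = 644 scores as independent. The true variance of the treatment difference is larger by the design effect DE = 1 + (14 − 1)ρ. The actual type I error is about 2[1 − Φ(1.96/√DE)]. This was checked by simulation under no treatment effect, with 4,000 runs per setting, a baseline covariate and no strata.

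| ρ (assumed) | DE | Type I error, formula | Simulated, no subject term | Simulated, between-subject error |
|---|---|---|---|---|
| 0.1 | 2.3 | 19.6% | 19.4% | 5.1% |
| 0.3 | 4.9 | 37.6% | 38.1% | 4.8% |
| 0.5 | 7.5 | 47.4% | 48.2% | 4.8% |
| 0.7 | 10.1 | 53.7% | 55.1% | 4.4% |

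**4. Dependence on the number of times.** With four times the formula gives 8.6%, 15.5%, 21.5% and 26.6% for the same correlations. With two times it gives 6.2%, 8.6%, 11.0% and 13.3%. With one time DE = 1 and there is no inflation.

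**The case against.** The strongest reply is that Section 9 calls the model a repeated-measures ANOVA, names subject as a factor and leaves it off the fixed-effects list. A statistician could take this to mean that subject is the error stratum, or that time varies randomly within subject. Under the error-stratum reading, treatment is tested against between-subject variation and the test is sound, as the last column of the table shows. This reply stands as far as it goes: the two failing readings are not the only ones. A reader might infer that the treatment standard error is necessarily too small under Section 9, and the text does not support that. It never says subject is fixed, nor that time is the only random effect allowed. But the valid reading requires a role for subject that the protocol does not give, while the role it does give goes to time.

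Second, the inflation figures come from a model without any subject term, although subject is named, and they need 14 scores per person and an assumed correlation. That is fair. They measure one literal reading and do not predict what will be done.

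Third, the 10-minute TNSS and the two 12-hour areas under the curve each give one post-intervention value per person, so no within-subject correlation arises. This also stands and limits the point to analyses over several times. Section 9 nevertheless includes time as a factor and states no single-time analysis for the primary endpoint.

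Fourth, a covariance structure or an interaction term may properly be left to an analysis plan that is not shown. Their absence alone would be no finding; calling planned times the random effect is a stated error.

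**Conclusion.** The point holds in a limited form. Section 9 gives the random role to planned assessment times and leaves subject's role undefined. The same sentence can therefore support a treatment test that cannot be estimated, one with a type I error of about 20% to 54%, or a valid one. The range rests on 46 completers, 14 modelled times, no subject term and an assumed equal correlation of 0.1 to 0.7. With two times it falls to about 6% to 13%, and with one value per person the problem disappears.

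A reader might also infer a large loss of power. If time meant Procedure 2 versus Procedure 3, with no treatment-by-time term, the main effect would average a pre-treatment and a post-treatment score, and a true difference of 1.5 would be estimated as 0.75. Without baseline adjustment, power would be about 54% at correlation 0.3 and 44% at 0.7 (here the pre/post correlation, also assumed). The protocol does not support this, because it puts the baseline score in the model. If that is the Procedure 2 score, the residual standard deviation of the average is ½ × 1.5 × √(1 − ρ²) = 0.75√(1 − ρ²), so the halving cancels in the test. With 23 per arm the standardised difference is √(23/2)/√(1 − ρ²), which gives power of about 94% at 0.3 and above 99% at 0.7. The estimate would still be halved, but no power loss follows. Using baseline as a covariate also argues against that reading of time.

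**What to change.** In Section 9, stop calling time a random effect. State instead that repeated scores are analysed with subject as the random effect, or with a named within-subject covariance. Time becomes a categorical fixed effect, and treatment, treatment-by-time, baseline score and the stratification variables are also fixed. An unstructured covariance over 14 times has 14 × 15/2 = 105 parameters, which is many for 46 people, so a structured form should be named if the covariance route is taken.

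For the primary 10-minute TNSS, name either the 10-minute treatment contrast from that model or an ANCOVA on the single post-intervention value, adjusted for baseline and strata. The ANCOVA is the simpler choice and needs no subject effect. Carry the same wording into the similar models for the other responses, and into the analysis plan if there is one.

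The cost is a sentence or two of text. Data collection, participant burden and the sample size of 46 completers do not change.
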